### 5.1.2. Corticosteroids (Corticosteroids Group)

**5.1.2.1. Administration and Tapering**

The initial dose of methylprednisolone is 2 mg/kg/day given twice daily for at least 7 days and then reduced ^[8]^. The dosage of methylprednisolone in the corticosteroids group is decreased gradually after CR and tapered off over 10 weeks as the following: dosage reduced to 1 mg/kg/day to 0.6 mg/kg/day, 0.4 mg/kg/day, 0.3 mg/kg/day, 0.25 mg/kg/day, and 0.18 mg/kg every 7 days, and then 0.1 mg/kg/day at week 4, 0.1 mg/kg every other day after 5 days, and stopped at week 10. CsA was administered intravenously at a dose of 2 mg/kg twice daily, targeting minimum concentration levels of 150–250 ng/mL. The recommended duration of CsA is 6 months.

**5.1.2.2. Criteria and Procedures for Dose Interruptions or Adjustments of** **Corticosteroids**

## The dosage of methylprednisolone in the corticosteroids group is decreased gradually after CR and tapered off over 10 weeks as the following: dosage reduced to 1 mg/kg/day to 0.6 mg/kg/day, 0.4 mg/kg/day, 0.3 mg/kg/day, 0.25 mg/kg/day, and 0.18 mg/kg every 7 days, and then 0.1 mg/kg/day at week 4, 0.1 mg/kg every other day after 5 days, and stopped at week 10.

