# 2. STUDY OBJECTIVES AND ENDPOINTS

| Primary Objective | Primary Endpoint |
| --- | --- |
| Compare the efficacy of ruxolitinib in combination with 1mg/kg methylprednisolone versus 2 mg/kg methylprednisolone alone in terms of overall response rate (ORR) at Day 28 in subjects with acute graft-versus-host disease (acute GVHD). | ORR at Day28, defined as the proportion of participants demonstrating a complete response (CR), or partial response (PR) |
| Secondary Objective | Secondary Endpoints |
| Compare additional response and longer-term efficacy outcomes between treatment cohorts. | Durable ORR at Day56, defined as the proportion of patients in each arm whose response on day 28 lasts until day 56 after randomization. |
|  | DOR at Month 6 for responders will be calculated. The DOR is defined from the time of the onset of response to loss of response. Subjects who died or discontinued will be censored at the  death date or the previous assessment. |
|  | Response duration, defined as the time from the first response to the first recurrence/progression of acute GVHD or additional immunosuppressants for GVHD. |
|  | NRM at Month 24, defined as the time from enrollment to death due to any causes other than hematologic disease relapse. |
|  | Cumulative incidence of relapse (CIR) at Month 24, defined as the proportion of subjects whose underlying hematologic disease relapses. |
|  | Disease-free survival (DFS) at Month 24, defined as the time from enrollment to relapse of primary disease or death from any causes, whichever occurred first. |
|  | Failure-free survival (FFS) at Month 24, defined as the time from randomization to disease relapse or progression, non-relapse mortality, or the addition of new therapy for acute GVHD. |
|  | Overall survival (OS) at Month 24, defined as the time from randomization to death due to any causes. |
| Assess the incidence and severity of adverse events (AEs) and serious adverse events. | Clinical safety data (eg, AEs, infections) will be tabulated and listed. |
| Evaluate the use and discontinuation of  corticosteroids. | Average and cumulative corticosteroid dose at Days 365; proportion of subjects who discontinue corticosteroids at Days 56 and 100. |
| Evaluate the use and discontinuation of  immunosuppressive medications. | Proportion of subjects who discontinue immunosuppressive medications at Days 365. |
| Evaluate the incidence of recurrent acute GVHD. | Incidence rate of recurrent acute GVHD through Month 12. |

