# 5. TREATMENT

## 5.1. Study Drugs

### 5.1.1. Ruxolitinib plus corticosteroids (Ruxolitinib Group)

**5.1.1.1. Administration and Tapering**

The initial dose of methylprednisolone is 1 mg/kg/day intravenously given in this arm for at least 7 days. The dosage of ruxolitinib is 5 mg PO QD. CSA will be administered intravenously at a dose of 2 mg/kg twice daily, targeting minimum concentration levels of 150–250 ng/mL. If GVHD response to treatment is assessed as PR/CR at 7 days, methylprednisolone will be tapered, followed by reduction and discontinuation of CSA and then ruxolitinib. The reduction of the methylprednisolone in the ruxolitinib group is gradual, suggesting it be tapered off over 6 weeks as follows: dosage reduced to 0.6 mg/kg/day, 0.4 mg/kg/day, 0.3 mg/kg/day, 0.25 mg/kg/day, and 0.18 mg/kg every 5 days, followed by 0.1 mg/kg/day at week 4, 0.1 mg/kg every other day after 5 days and stopped at week 6. After steroid discontinuation and CR or stable PR maintained for 6 weeks, CSA is tapered over 60 days. After CSA discontinuation and no presence of recurrent GVHD, ruxolitinib is tapered off over 90 days, which is totally maintained for approximately 6 months ^[2]^.

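### Control-arm methylprednisolone taper: the 7-day steps take 42 days, which contradicts the week-4 mark for the step to 0.1 mg/kg/day

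*Protocol*

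**What the plan says.** Protocol section 5.1.2.1 sets the control arm's initial methylprednisolone dose at 2 mg/kg/day, "given twice daily for at least 7 days and then reduced". The dose is then "decreased gradually after CR and tapered off over 10 weeks".

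Section 5.1.2.2 repeats the taper. It lists six levels that begin at 1 mg/kg/day, and gives the last level, the step length and the next step as "and 0.18 mg/kg every 7 days, and then 0.1 mg/kg/day at week 4". Alternate-day dosing follows 5 days later, with the stop at week 10. The Synopsis carries the same wording, so the text stands in three places.

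The ruxolitinib arm (section 5.1.1.1) has five levels that begin at 0.6 mg/kg/day. Its corresponding clause reads "and 0.18 mg/kg every 5 days, followed by 0.1 mg/kg/day at week 4", and its stop is at week 6.

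Section 2 makes average and cumulative corticosteroid dose at Day 365 a secondary endpoint, together with the "proportion of subjects who discontinue corticosteroids at Days 56 and 100". Section 5.3 says that corticosteroid dose changes and interruptions will be documented and monitored, but that compliance with corticosteroids will not be calculated.

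**The concern.** The two tapers share the same week-4 mark, although the control arm has one more level and a longer step. A site that follows the step length will be at a different dose from a site that follows the week label. The text gives no rule for choosing between them and does not say from which day weeks are counted.

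The comparator is therefore not uniquely defined from about week 4 onward. Corticosteroid exposure is itself an endpoint, and the ambiguity lies in one arm only, so the between-arm difference in cumulative dose would partly depend on which clause each site applied. No planned compliance measure for corticosteroids would bring such a divergence to light.

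**Working it through.** **Inputs.** Control levels before 0.1 mg/kg/day: 1, 0.6, 0.4, 0.3, 0.25, 0.18 mg/kg. Step: 7 days. Then 5 days at 0.1 mg/kg/day, then 0.1 mg/kg every other day, stop at week 10 (sections 5.1.2.1 and 5.1.2.2). Ruxolitinib arm: five levels, 5-day steps (section 5.1.1.1).

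**Check of the method.** Start of the 0.1 mg/kg/day step = number of preceding levels × step length. In the ruxolitinib arm this is 5 × 5 = 25 days, which falls in week 4 (days 22-28) counted from taper start, as stated there.

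**Control arm, same formula.**

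| Reading | Days before 0.1 mg/kg/day | Week in which it starts |
|---|---|---|
| 6 levels × 7 days, from taper start | 42 | 7 |
| 5 levels × 7 days (1 to 0.6 as one step) | 35 | 6 |
| 6 levels × 7 days, from treatment start (+7) | 49 | 8 |
| 5 levels × 7 days, from treatment start (+7) | 42 | 7 |
| 6 levels × 5 days (the other arm's step) | 30 | 5 |

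None gives week 4. To fit six levels into 28 days, each step could last at most 28/6 = 4.7 days.

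**Is the 10-week total consistent?** From taper start, 42 + 5 = 47 days, which leaves 70 − 47 = 23 days of alternate-day dosing before the stop. Levels, interval and total fit together; only the week-4 mark does not fit with them.

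**Cumulative dose.** This is illustrative and not in the documents. Assume exactly 7 days at 2 mg/kg/day (7 × 2 = 14 mg/kg), taper from Day 8, and alternate-day dosing that begins with a dosing day.

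Weeks counted from taper start (70 taper days, last day Day 77):
- All steps: 14 + 7 × (1 + 0.6 + 0.4 + 0.3 + 0.25 + 0.18) + 5 × 0.1 + 12 × 0.1 = 14 + 19.11 + 0.5 + 1.2 = 34.8.
- Drop at the end of week 4 (after 28 taper days): 14 + 7 × 2.3 + 0.5 + 19 × 0.1 = 14 + 16.1 + 0.5 + 1.9 = 32.5, which is 7% lower.
- Drop at the start of week 4 (after 21 taper days): 14 + 7 × 2.0 + 0.5 + 22 × 0.1 = 14 + 14.0 + 0.5 + 2.2 = 30.7, which is 12% lower.

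Weeks counted from treatment start (63 taper days, last day Day 70):
- All steps: 14 + 19.11 + 0.5 + 8 × 0.1 = 34.4.
- Drop at the end of week 4 (from Day 29): 14 + 14.0 + 0.5 + 1.9 = 30.4, which is 12% lower.
- Drop at the start of week 4 (from Day 22): 14 + 7 × 1.6 + 0.5 + 2.2 = 14 + 11.2 + 0.5 + 2.2 = 27.9, which is 19% lower.

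**Dose on Day 28.** On the step reading, Days 22-28 are the third taper week, at 0.4 mg/kg/day. With weeks counted from taper start, week 4 is Days 29-35, so the week-4 reading also gives 0.4 on Day 28. A difference on Day 28 needs weeks counted from treatment start and a drop before the end of that week.

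**Steroid discontinuation.** Both readings end at the same week-10 stop: Day 70 from treatment start, or Day 77 from a taper that begins on Day 8. A patient on schedule is on steroid at Day 56 and off by Day 100 either way.

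**The case against.** The strongest reply is that this is one faulty label in an otherwise coherent schedule. The levels, the 7-day interval and the 10-week total agree, treating doctors are to be trained uniformly (section 4.2), and dose changes are documented and monitored (section 5.3). Nothing in the document shows that sites diverged. All of that stands and limits the weight of the point. It does not remove the contradiction: uniform training needs one schedule to train on, and the protocol does not say which clause governs.

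Several stronger conclusions are tempting but not supported:

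- A reader might infer that the control regimen is undefined at the Day 28 primary assessment, so that the ORR comparison is biased. The text describes the taper as "decreased gradually after CR and tapered off over 10 weeks as the following", which makes taper start the natural origin; on that count both readings give the same dose on Day 28. A later complete response (CR) pushes the divergence further past Day 28.
- A reader might infer that the Day 56 and Day 100 discontinuation proportions are affected. The shared week-10 stop leaves them essentially unchanged.
- A reader might see a second contradiction between the minimum of 7 days and tapering after CR. These can be read together as a minimum duration plus a condition.
- A reader might take about 20% as the general size of the dose gap. A gap of 19% arises only with weeks counted from treatment start and the earliest switch.
- A reader might infer that the mark was carried over from the ruxolitinib text, or that a duration of four weeks was meant (6 + 4 = 10 weeks). Both are guesses that the wording does not confirm.

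**Conclusion.** The point holds in a narrow form. In the control arm, the 7-day steps and the week-4 mark for 0.1 mg/kg/day contradict each other under every reading tried: 42 days are needed, or 35 on the most lenient count of levels at the stated step length. The contradiction is confined to that mark; the 10-week total is not in conflict.

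Its size is a difference of 7-12% in cumulative methylprednisolone over the initial course if weeks run from taper start, and 12-19% if they run from treatment start. This rests on 7 days at 2 mg/kg/day, taper from Day 8 and full adherence to one reading or the other. A longer initial period would change the totals.

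The consequences fall on the secondary endpoint of average and cumulative corticosteroid dose and on uniform delivery of the comparator. The sample size is untouched, and any effect on Day 28 ORR is indirect and conditional on the origin of the week count. It is worth correcting, but does not threaten the primary analysis.

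**What to change.** Replace the taper text in the Synopsis and sections 5.1.2.1 and 5.1.2.2 with a single day-to-dose schedule in which step lengths and week labels agree. State the day from which weeks 4 and 10 are counted. Report corticosteroid dose received by arm against that schedule, so that departures are visible even though no compliance figure is calculated. Which of the conflicting elements should change is for the sponsor's clinicians.

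The cost is a wording clarification and a memo to sites. Dose changes are already to be documented under section 5.3, so no new data collection is needed.

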## 5.2. Criteria for Permanent Discontinuation of Study Drug

The occurrence of unacceptable toxicity not caused by the underlying disease or malignancy will be presumed to be related to study drug treatment and will require that the study drug be permanently discontinued. Unacceptable toxicity is defined as follows:

- Occurrence of an AE that is related to treatment with the study drug that, in the

judgment of the investigator or the sponsor's medical monitor, compromises the

subject's ability to continue study-specific procedures or is considered not to be in the

subject's best interest.

- Persistent AE requiring a delay of therapy for more than 14 days, unless a greater

delay has been approved by the sponsor.

## 5.3. Treatment Compliance

Treatment compliance with all study-related medications should be emphasized to the subject by the site personnel, and appropriate steps should be taken to optimize compliance during the study. Ruxolitinib compliance will be calculated, by the sponsor, based on the drug accountability documented by the site staff and monitored by the sponsor/designee (tablet counts). Subjects will be instructed to bring all study-related medications with them to each study visit in order for site personnel to conduct tablet counts to assess study drug accountability. The drug accountability documentation will be used by the sponsor to calculate treatment compliance. Although commercial supplies of corticosteroids will be used, dose changes and interruptions will also be documented in the medical record and monitored by the sponsor or its designee. As corticosteroid dose strengths and administration types will vary, compliance with corticosteroids will not be calculated.

## 5.4. Withdrawal of Subjects from Study Treatment

The decision to discontinue study treatment will not constitute study completion. In the event that the decision is made to discontinue study treatment, the treatment period will be considered complete, and the follow-up period will begin.

### 5.4.1. Withdrawal Criteria

Subjects must be withdrawn from study treatment for the following reasons:

- The subject has experienced an unacceptable toxicity.
- Relapse of underlying malignancy.
- The subject is unable to tolerate ruxolitinib at a dose of 5 mg QD.
- Additional systemic therapy is required for GVHD progression or lack of response, including corticosteroid doses greater than those used on Study Day 1.
- Further participation would be injurious to the subject's health or well-being, in the investigator's medical judgment.
- The subject becomes pregnant.
- Consent is withdrawn.
- The study is terminated by the sponsor.

A subject **may** be withdrawn from study treatment as follows:

- If, during the course of the study, a subject is found not to have met eligibility criteria, then the medical monitor, in collaboration with the investigator, will determine whether the subject should be withdrawn from the study.
- If a subject is noncompliant with study procedures or study drug administration in the investigator's opinion, the sponsor should be consulted for instruction on handling the subject.

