| \| **Primary Objective** \| **Primary Endpoint** \| \| --- \| --- \| \| Compare the efficacy of ruxolitinib in combination with corticosteroids versus corticosteroids in terms of overall response rate (ORR) at Day 28 in subjects with acute graft-versus-host disease (acute GVHD). \| ORR at Day28, defined as the proportion of participants demonstrating a complete response (CR), or partial response (PR) \| \| **Secondary Objective** \| **Secondary Endpoints** \| \| Compare additional response and longer-term efficacy outcomes between treatment cohorts. \| Durable ORR at Day56, defined as the proportion of patients in each arm whose response on day 28 lasts until day 56 after randomization. \| \| DOR at Month 6 for responders will be calculated. The DOR is defined from the time of the onset of response to loss of response. Subjects who died or discontinued will be censored at the  death date or the previous assessment. \| \| Response duration, defined as the time from the first response to the first recurrence/progression of acute GVHD or additional immunosuppressants for GVHD. \| \| NRM at Month 24, defined as the time from enrollment to death due to any causes other than hematologic disease relapse. \| \| Cumulative incidence of relapse (CIR) at Month 24, defined as the proportion of subjects whose underlying hematologic disease relapses. \| \| Disease-free survival (DFS) at Month 24, defined as the time from enrollment to relapse of primary disease or death from any causes, whichever occurred first. \| \| Failure-free survival (FFS) at Month 24, defined as the time from randomization to disease relapse or progression, non-relapse mortality, or the addition of new therapy for acute GVHD. \| \| Overall survival (OS) at Month 24, defined as the time from randomization to death due to any causes. \| \| Assess the incidence and severity of adverse events (AEs) and serious adverse events. \| Clinical safety data (eg, AEs, infections) will be tabulated and listed. \| \| Evaluate the use and discontinuation of  corticosteroids. \| Average and cumulative corticosteroid dose at Days 365; \| \| Evaluate the use and discontinuation of  immunosuppressive medications. \| Proportion of subjects who discontinue immunosuppressive medications at Days365. \| \| Evaluate the incidence of recurrent acute GVHD \| Incidence rate of recurrent acute GVHD through Month 24. \| \| Evaluate the incidence of cGVHD. \| Incidence rate of cGVHD at Month 24. \| \| **Overall Study Design:**  This trial is an open-label, multicenter, prospective randomized two-arm phase II study comparing the efficacy and safety of ruxolitinib plus methylprednisolone (1 mg/kg) vs. methylprednisolone (2 mg/kg) alone. The biomarkers of acute GVHD, such as sST2, sTNFR1, IL-6, IL-8, and REG3α will be tested at acute GVHD onset. Patients with newly diagnosed intermediate-risk or high-risk acute GVHD, as defined by Minnesota acute GVHD risk score and the biomarker score will be included. The treatment efficacy will be evaluated with respect to the level of biomarkers and clinical manifestations. Written informed consent must be obtained from the patients before enrollment in the study. The consent form and related materials are available from the corresponding author on request.  **Study Population:**  Eligible patients with intermediate-risk or high-risk acute GVHD graded according to the modified Glucksberg criteria, Minnesota acute GVHD risk score and the biomarker score and untreated with systemic acute GVHD therapy will be enrolled in this study.  **Key Inclusion Criteria:**   - Male or female, 14 to 65 years old. - Have undergone first allogeneic hematopoietic stem cell transplantation (allo-HSCT) from any donor source using bone marrow, peripheral blood stem cells, or cord blood for hematologic malignancies. - Develop a de novo acute GVHD, defined as intermediate- or high-risk using the Minnesota acute GVHD risk score and MAGIC biomarker algorithm.   **Key Exclusion Criteria:**   - Has received more than one allogeneic stem cell transplant. - Female patients with pregnant or breast-feeding. - Has Acquired Immune Deficiency Syndrome (AIDS), or hepatitis B/C infection, uncontrolled bacterial, fungal, or viral infections. - Allergies to ruxolitinib. - Vital organ dysfunction unrelated to GVHD, including persistent bilirubin abnormalities or severe heart and respiratory diseases. - Relapse of the primary disease or graft rejection after transplantation. - Presence of GVHD overlap syndrome. - Presence of cGVHD or associated clinical signs or DLI-induced acute GVHD or interferon. - Previous history of JAK1/2 inhibitor treatment after transplantation, except JAK inhibitors administered before the transplantation. - absolute neutrophil count (ANC) <0.5×10^9^/L or platelet count (PLT) < 20×10^9^/L - Serum creatinine > 2.0 mg/dL or creatinine clearance < 40 mL/min measured or calculated by Cockroft-Gault equation. - Patients with poor compliance should not be included in the study based on the judgment of the research team, for example if they refused to take medicine at will many times during the previous treatment.   **Study Drug, Dosage, and Mode of Administration:**  **Ruxolitinib plus corticosteroids treatment (ruxolitinib group):**  The initial dose of methylprednisolone is 1 mg/kg/day intravenously given in this arm for at least 7 days. The dosage of ruxolitinib is 5 mg PO QD. CSA will be administered intravenously at a dose of 2 mg/kg twice daily, targeting minimum concentration levels of 150–250 ng/mL. If GVHD response to treatment is assessed as PR/CR at 7 days, methylprednisolone will be tapered, followed by reduction and discontinuation of CSA and then ruxolitinib. The reduction of the methylprednisolone in the ruxolitinib group is gradual, suggesting it be tapered off over 6 weeks as follows: dosage reduced to 0.6 mg/kg/day, 0.4 mg/kg/day, 0.3 mg/kg/day, 0.25 mg/kg/day, and 0.18 mg/kg every 5 days, followed by 0.1 mg/kg/day at week 4, 0.1 mg/kg every other day after 5 days and stopped at week 6. After steroid discontinuation and CR or stable PR maintained for 6 weeks, CSA is tapered over 60 days. After CSA discontinuation and no presence of recurrent GVHD, ruxolitinib is tapered off over 90 days, which is totally maintained for approximately 6 months.  **Corticosteroid treatment (corticosteroids group):**  The initial dose of methylprednisolone is 2 mg/kg/day given twice daily for at least 7 days and then reduced. The dosage of methylprednisolone in the corticosteroids group is decreased gradually after CR and tapered off over 10 weeks as the following: dosage reduced to 1 mg/kg/day to 0.6 mg/kg/day, 0.4 mg/kg/day, 0.3 mg/kg/day, 0.25 mg/kg/day, and 0.18 mg/kg every 7 days, and then 0.1 mg/kg/day at week 4, 0.1 mg/kg every other day after 5 days, and stopped at week 10. CsA was administered intravenously at a dose of 2 mg/kg twice daily, targeting minimum concentration levels of 150–250 ng/mL. The recommended duration of CsA is 6 months.  In both arms, for refractory acute GVHD, i.e., the progression of GVHD after 3 days of therapy, no improvement within 7 days, or no CR after 14 days of therapy, the second-line therapy will be started. For refractory acute GVHD or recurrent acute GVHD, basiliximab may be used as second-line therapy, and other alternative drugs included methotrexate or mesenchymal stem cells may be used at the researcher’s decision. For refractory acute GVHD, methylprednisolone is discontinued and CsA is continued in both arms. Prolonged maintenance of ruxolitinib is used in the ruxolitinib group. A standardized follow-up booklet is given to each enrolled patient for recording the dose, frequency, and administration method of the drugs. **Estimated Duration of Participation:** Subject participation is expected to average 24 months, which includes the following:   - A screening period lasting up to 28 days. - A treatment period lasting as long as the subject is benefiting from treatment. - A safety follow-up period lasting 180 days after treatment ends. - A survival follow-up period lasting until death or study withdrawal. \| \| \| **Estimated Number of Subjects:** 198 subjects. \| \| \| **Principal Coordinating Investigator:** [name] \| \| \| **Statistical Methods:**  The sample size is calculated according to the primary endpoint (ORR) of the study. Based on our published phase I study of 32 acute GVHD patients who received steroids as first-line therapy, an expected proportion of 55% for the patients treated with corticosteroids only was established. Based on our published data of patients with acute GVHD grade I–IV who received steroid-ruxolitinib (5 mg/day) as first-line therapy, the ORR was 82.05%. Patients with acute GVHD grade I were also included in the phase I analysis. Thus, an expected proportion of 75% for the patients treated with steroid-ruxolitinib (5mg/day) was established. This study is planned to detect a response difference between treatment arms at a two-sided significance level α=5% with a power of 1-β=80%. The sample size was estimated using PASS software based on the primary endpoint (ORR). Allowing a withdrawal rate of 10%, 198 patients (99/group) will be required.  Continuous data are described as median with interquartile range (IQR) or mean and standard deviation (SD) according to the normality of distribution. The categorical data are described as n (%). The ORR was calculated with its 95% confidence interval (CI) and compared by the stratified Cochran–Mantel–Haenszel test. Additionally, a logistic regression model, which included aGVHD risk (high vs. intermediate), and disease status before transplantation (CR vs. no CR) as covariates, was established to explore the association between treatment and ORR on day 28. Post-hoc subgroup analysis was performed by biomarker risk, age and GVHD grade, although these were not prespecified in the protocol. The cumulative incidence of recurrent aGVHD was analysed using the Fine and Gray test in a competing risk framework. The Kaplan–Meier method was used to estimate the ORR on day 56, OS, DFS, and FFS, and the log-rank test was used to evaluate the difference between the groups. The cumulative incidence rates of NRM and relapse were estimated using a competing risk model and compared using the Fine and Gray test. A Cox proportional hazard regression model was used for multivariable regression analysis for OS and DFS. Multivariable regression analysis was performed for NRM using the Fine–Gray proportional hazard regression for competing events. The following variables were included in the univariable analysis: primary disease, cytogenetic risk, age and gender of the donor and recipient, source of graft, treatment arm, aGVHD risk, and disease status before transplantation. Variables with P<0.1 in univariate analysis or variables known to influence the outcomes were included in the multivariable analysis. Competing events were defined as follows: for GVHD, death without the event; for relapse, death without relapse; and for NRM, relapse. Any difference for which the two-sided P<0.05 was considered statistically significant. All analyses were carried out using SPSS 22.0 software (IBM Corporation, Armonk, NY, USA) or R version 4.1.2 (www.cran.r-project.org). All statistical analyses were based on the intend to treat set. \| \| | |

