In view of the durable response and safety observed in previous ruxolitinib studies, the clinical benefits of ruxolitinib outweigh the risks of treatment. Retrospective data indicated that prolonged maintenance of ruxolitinib is allowed even after refractory GVHD and responses in acute GVHD can be observed at 11 weeks after ruxolitinib treatment ^[4, 15]^. Prolonged maintenance of ruxolitinib is allowed in the case of recurrent acute GVHD or refractory acute GVHD (the progression of GVHD after 3 days of therapy, no improvement within 7 days, or no CR after 14 days of therapy) after ruxolitinib plus corticosteroid treatment ^[4]^. If patients in the ruxolitinib group do not reach the CR by day 28, ruxolitinib will also be continued beyond 6 months in the event of no contraindications. Tapering of ruxolitinib is permitted after day 56 in patients who have a response to the second line therapy for recurrent acute GVHD or refractory acute GVHD. An additional follow‐up through at least day 180 is required to determine the durability of treatment responses ^[27]^. During the trial, drug interactions should be examined first before adding new agents in order to reduce the potential effects of other drugs on ruxolitinib. Fluconazole >200 mg/day is prohibited as it disrupts the metabolism of ruxolitinib.

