### 5.4.2. Withdrawal Procedures

In the event that the decision is made to permanently discontinue the study drug, the subject will be withdrawn from the study and the EOT visit should be conducted. Reasonable efforts should be made to have the subject return for a follow-up visit. The last date of the last dose of study drug and the reason for subject withdrawal will be recorded in the eCRF.

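### The protocol conflicts with itself on whether a patient who starts second-line GVHD therapy stays on ruxolitinib (5.4.1 against the Synopsis and 5.1.1.1) and stays in the study (5.4.2 against 5.4)

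*Protocol*

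**What the plan says.** **Ruxolitinib after failure.** Section 5.4.1 opens its list with "Subjects must be withdrawn from study treatment for the following reasons", and one listed reason is "Additional systemic therapy is required for GVHD progression or lack of response, including corticosteroid doses greater than those used on Study Day 1". The Synopsis defines refractory acute GVHD by any of three triggers: worsening after 3 days of treatment, lack of improvement by day 7, or CR not reached by day 14. It has second-line therapy started in both arms for such patients. It then stops methylprednisolone, continues CsA and adds "Prolonged maintenance of ruxolitinib is used in the ruxolitinib group". Section 5.1.1.1 agrees with the Synopsis: "Prolonged maintenance of ruxolitinib is allowed in the case of recurrent acute GVHD or refractory acute GVHD". It also states "Tapering of ruxolitinib is permitted after day 56 in patients who have a response to the second line therapy", which presupposes that ruxolitinib is still being given during second-line therapy.

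**Study status after stopping.** Section 5.4 says that a decision to stop study treatment is not study completion and that the follow-up period begins. Section 5.4.2 says that on permanent discontinuation of study drug "the subject will be withdrawn from the study and the EOT visit should be conducted".

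**Staging after stopping.** Section 7.5.1 sets weekly grading for the first 8 weeks from randomization. Its post-withdrawal grading, and the 28-day GVHD visits in 6.5.2, are set only for patients who stopped for reasons other than GVHD progression. Section 6.5.3 gives the remaining patients a contact at least every 8 weeks for survival and new GVHD therapy.

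**The concern.** For a ruxolitinib-arm patient who progresses or does not improve and then starts second-line therapy, one section ends study treatment and two continue it. The protocol therefore gives two incompatible accounts of the experimental strategy after failure, although the Month 24 outcomes (FFS, OS, NRM) compare strategies.

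Three practical matters hang on it:

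- **End-of-treatment date.** It starts the 180-day safety follow-up in 6.5.1 and the 12-month limit in 6.5.2.
- **Adverse event window.** Sections 6.5.1, 7.4.1.2 and 7.4.2.2 tie reporting to the last dose of study drug. If ruxolitinib continues after withdrawal from study treatment, it is unclear whether those doses extend the window.
- **Day 28 and Day 56 staging.** All three refractory triggers can be met before Day 28, so a site that follows 5.4.2 literally could stop staging before the primary endpoint is read.

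**Working it through.** The point is a comparison of texts. The arithmetic only gives its scale.

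**Step 1: which patients meet both rules (ruxolitinib arm).**

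| Situation | 5.4.1 | Synopsis / 5.1.1.1 | Conflict |
|---|---|---|---|
| Progression after 3 days, second-line started | withdraw from study treatment | ruxolitinib continues | clear |
| No improvement by day 7, second-line started | withdraw | ruxolitinib continues | clear |
| PR but no CR at day 14, second-line started | trigger met only if PR counts as lack of response | ruxolitinib continues | partial |
| No CR by day 28, no added therapy | trigger not met | "ruxolitinib will also be continued beyond 6 months in the event of no contraindications" | none from this sentence alone |

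No section labels the continued ruxolitinib as off-study or exempts it from 5.4.1. In the control arm there is no ruxolitinib to continue, so this conflict does not arise.

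**Step 2: study status (both arms).** Section 5.4 leads to follow-up, while 5.4.2 leads to withdrawal from the study. Sections 6.5.2 and 7.5.1 do not settle it for progressors, because their post-withdrawal grading excludes them. The general weekly schedule in 7.5.1 does reach Day 56, but nothing says that it overrides 5.4.2.

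**Step 3: the plan's own sample size.** Inputs from 4.5.2: 55% and 75%, two-sided 5%, power 80%, 10% withdrawal.

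n = [1.96 × √(2 × 0.65 × 0.35) + 0.8416 × √(0.55 × 0.45 + 0.75 × 0.25)]² / 0.20² = (1.322 + 0.555)² / 0.04 ≈ 88.1, so 89 per group. Then 89 / 0.90 = 98.9, so 99 per group and 198 in total. The stated figure reproduces and is not in dispute.

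**Step 4: rough scale.** Planned Day 28 non-responders: 99 × 0.25 = 24.75, about 25 (ruxolitinib), and 99 × 0.45 = 44.55, about 45 (control).

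**Step 5: what outcome-related loss could do (my assumption, not in the documents).** Suppose a fraction f of non-responders is unstaged at Day 28 and either dropped or imputed as if they resembled the staged patients in their arm. The estimated rate is then p / (1 − (1 − p)f).

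| f ruxolitinib | f control | Missing | Estimated ORR | Difference |
|---|---|---|---|---|
| 0 | 0 | 0% / 0% | 75.0% vs 55.0% | 20.0 points |
| 0.2 | 0.2 | 5% / 9% | 0.75/0.95 = 78.9% vs 0.55/0.91 = 60.4% | 18.5 |
| 0.4 | 0.4 | 10% / 18% | 0.75/0.90 = 83.3% vs 0.55/0.82 = 67.1% | 16.3 |
| 0 | 0.4 | 0% / 18% | 75.0% vs 67.1% | 7.9 |
| 0.4 | 0 | 10% / 0% | 83.3% vs 55.0% | 28.3 |

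Each affected arm's rate rises, but the difference can move either way. At f = 0.4 in both arms, average missingness is (10% + 18%) / 2 = 14%, above the 10% ceiling that section 8.4 expects.

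**The case against.** The strongest reply is that follow-up of failures is largely in place. Section 5.4 keeps them in follow-up. The list in 5.4.2 requires an end-of-treatment visit, a recorded reason and safety follow-up, and ends data collection only when consent to follow-up is actively withdrawn. Section 6.5.3 covers survival and new therapy, and the weekly grading in 7.5.1 runs from randomization. The Synopsis states intention-to-treat, 8.4 includes all randomized participants, and FFS already counts new GVHD therapy as an event. The 5.4.2 phrase may be loose drafting, since its next sentence asks for a follow-up visit. This stands, and it rules out four stronger readings that a reader might infer:

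- **That data capture for failures is undefined.** It is partly defined. What is unsettled is study status and organ staging after withdrawal for progression.
- **That ORR is inflated.** A failure with a documented reason can be counted as a non-responder, and a Day 28 non-responder already fails the Day 56 endpoint. Bias arises only if such patients are unstaged and handled as missing.
- **That at least 25 ruxolitinib and 45 control patients are caught.** Non-response at Day 28 is not the same as starting second-line therapy, and controls are touched only by the study-status wording.
- **That recurrent GVHD is equally in conflict.** The 5.4.1 trigger does not name recurrence, and recurrence after a completed taper has its own re-treatment phase in 6.4.

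One might also read the continued ruxolitinib as care outside the study. No section says so, and that reading would still leave the reporting window for those doses open.

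**Conclusion.** The point holds in two parts. (a) Section 5.4.1 contradicts the Synopsis and 5.1.1.1 on ruxolitinib once second-line therapy starts. The contradiction is clear for progression and for no improvement, and partial for a patient in PR without CR at day 14. (b) Section 5.4.2 contradicts 5.4 on study status in both arms, and 6.5.2 and 7.5.1 leave post-withdrawal grading unset for progressors, so sites may differ on staging failures at Days 28 and 56.

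The certain consequences are an ambiguous end-of-treatment date and an ambiguous adverse event window. Loss of response data and bias in ORR are possible but not demonstrated. The illustrative range of 8 to 28 points around the planned 20 rests wholly on the assumed loss and on treating it as ignorable. The number of patients affected cannot be derived from the documents. The sample size is unaffected.

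**What to change.** 1. Reconcile 5.4.1, 5.1.1.1 and the Synopsis into one rule for patients who start second-line therapy, including those in PR without CR at day 14. Which clinical rule applies is for the sponsor to decide.
2. State whether ruxolitinib given after second-line therapy starts counts as study treatment for the end-of-treatment date and for AE and SAE reporting.
3. Correct 5.4.2 to refer to withdrawal from study treatment, not from the study.
4. State in 6.5.2 and 7.5.1 that scheduled GVHD staging through Day 56, and follow-up to Month 24, continue in both arms after second-line therapy starts unless consent to follow-up is withdrawn.

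The cost is a wording amendment and a note to sites. The staging schedule and survival contacts already exist, so the added burden is small, and neither the sample size nor the endpoint definitions change.
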